### Clinical Trial Design

A phase I/IIa double-blind, parallel-group, single-institute trial initiated by a medical investigator

## Study Population

Outpatients with fluctuating hearing diagnosed as PDS in *SLC26A4* genetic testing are eligible to participate if all of the inclusion criteria described below are met, and if none of the exclusion criteria below are met.

[Inclusion Criteria]

1) Aged at least seven and below fifty years at the time of consent

2) Confirmed PDS-positive by genetic testing such as Sanger Sequencing

3) Report of subjective symptoms of fluctuating hearing disorder in a medical interview for case registration

4) Subjective symptoms of episodes of hearing loss and/or dizziness/vertigo within one year prior to the case registration

5) Had undergone inner-ear function testing at least three times, including standard pure-tone audiometry, performed with an interval of one day or longer, within six months prior to the case registration

6) Voluntary informed consent in writing obtainable from the patient or the patient’s legally acceptable representative

[Rationale]

1) To allow participation of patients of a wide range of ages, in consideration of patient demographics

2) through 5) To select patients who are considered to be appropriate for evaluation of investigational product efficacy

6) To ensure ethical conduct of the clinical trial

[Exclusion Criteria]

1) Prior use of molecular targeted drugs related to mTOR pathway, such as sirolimus, other mTOR inhibitors (e.g., everolimus) and tyrosine kinase (e.g., bevacizumab, sorafenib)

2) History of hypersensitivity to sirolimus, including sirolimus derivatives, and its additive agents

3) HBs antigen-positive, HBs antibody-positive, HBc antibody-positive, or active hepatitis C (HCV antibody-positive patients with inactive hepatitis and with normal-range values of liver function do not apply.)

HBs antigen-positive patients for which the cause is presumed to be due to vaccination against hepatitis B may participate in this clinical trial.

4) Severe blood abnormalities or hepatic dysfunction that demonstrate conditions shown below.

| Items | Value |
| --- | --- |
| AST or ALT | 100 IU/L or higher |
| Hematocrits | below 30% |
| Platelet count | below 80,000/mm^3^ |
| Absolute neutrophil count | below 1,000/mm^3^ |
| Total white blood cell count | below 3,000/mm^3^ |

5) Patients with poorly controlled dyslipidemia

Serum triglyceride of 500 mg/dL or higher or LDL cholesterol level of 190 mg/dL or higher despite being under treatment for dyslipidemia.

6) Severe renal impairment

Estimated glomerular filtration rate (eGFR) lower than 30 mL/min/1.73 m^2^

7) Immunodeficiency such as HIV or primary immunodeficiency

8) Inability to take investigational products in tablet form, or gastrointestinal dysfunction with risks of malabsorption of sirolimus

9) History of having surgery within eight weeks prior to the registration (any surgery that requires invasion of the body or suture with three or more stitches, including biopsy)

10) Female patients who are pregnant, potentially pregnant, or breastfeeding. Male or female patients who decline to consent to contraception during the trial

Contraceptive methods: Combination of condoms and spermicide; combination of condoms and diaphragms with spermicide; oral contraceptive; intrauterine contraceptive device; or other methods

11) Need to take medications that influence CYP3A4 activation after the administration of investigational products

12) Pulmonary interstitial opacity

13) Diagnosis by the attending physician during the screening phase or from previous observations from hearing tests that the hearing loss is fixed rather than fluctuating

14) Participation in other clinical research and/or trials within six months prior to the date of consent, with the exception of Analysis of Diseases in Otorhinolaryngology Using iPS Cells (approval No. 20140172)

15) Other conditions that the principal investigator or subinvestigator deems inappropriate

[Rationale]

1) through 7), 9) through 12), and 15) To ensure patients’ safety and to assess safety appropriately

8) The situation disturbs prediction of pharmacokinetics of the investigational products.

13) and 14) These may influence analysis of the investigational products.

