# Procedures of the Trial

## Registration of Patients

The principal investigator or subinvestigator will obtain written informed consent from patients who are thought to satisfy the inclusion criteria, or their legally acceptable representatives, and register the patients in accordance with the following procedures:

| 1) Selection of patients | |
| --- | --- |
|  | The principal investigator or subinvestigator will carefully examine whether respective patients are eligible to participate in the clinical trial, taking account of patients’ health conditions, symptoms, age, gender, relationship with the principal investigator, and participation in any other clinical trials. |
| 2) Informed consent | |
|  | The principal investigator or subinvestigator will provide information pertinent to the clinical trial to patients who are thought to satisfy the inclusion criteria of the trial, and obtain written informed consent from the patients or their legally acceptable representatives. |
| 3) Assignment of subject identification code | |
|  | Subsequent to informed consent, required data will be entered into the electronic case report forms, and subject identification code numbers will be assigned. This will be recorded on the subject screening list. The code numbers will be used for identification of the patients throughout this trial. |
| 4) Screening | |
|  | Patients will go through screening two weeks (+/- seven days) before the initial intake of the investigational products. |
| 5) Confirmation of eligibility by the principal investigator or subinvestigator | |
|  | Prior to starting the first dose of the investigational products, the principal investigator or subinvestigator will judge whether patients satisfy the inclusion criteria, based on the assessment during the screening phase, using the eligibility check sheet. |
| 6) Registration of subjects and assignment of investigational products (V1) | |
|  | Patients whose eligibility to participate in the trial is confirmed in 5) will be registered and have investigational products assigned via the electronic case report form. Unique code numbers (pharmaceutical agent numbers) will be assigned to the registered subjects. This will be recorded in the subject screening log.  Patients whose eligibility is denied in 5) will be treated as screen failures. Screen failures will be recorded in the remarks column of the subject screening log. |

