# Prohibited Concomitant Medications and Therapies

1) In principle, subjects will be prohibited from taking any of the following medications unless the principal investigator or subinvestigator allows the concomitant use in response to acute exacerbation:

ATP solution (e.g., Adetphos^Ⓡ^), Vitamin B12 solution (e.g., Methycobal^Ⓡ^), Betahistine (e.g., Merislon), and medications that improve microcirculation (e.g., Kallikrein).

2) Subjects will be prohibited from concomitant use of medications described below.

Sirolimus is metabolized by a drug-metabolizing enzyme CYP3A4, and is a substrate for P-glycoprotein. Sirolimus itself is an inhibitor of CYP3A4. Subjects are thus prohibited from taking any of the medications and foods listed below throughout their participation in this clinical trial, i.e., from the initial administration of investigational products (V1) to the end of the administration (V12).

| Influencing factors | Medications and food | Rationale |
| --- | --- | --- |
| 1) Inhibition of mTOR | everolimus; temsirolimus | The products have the same mechanism of action as the investigational products, which would disturb efficacy analysis. |
| 2) Influence on the assessment of the disease studied | aminoglycoside class of antibiotics; platinum-based drugs | Ototoxicity of the products could exacerbate inner ear disorder.  (Topical administration is allowed.) |
| 3) Live vaccines | live vaccines (e.g., measles, mumps, rubella, oral polio, BCG) | The immunosuppresive properties of sirolimus may cause proliferation of microorganisms in live vaccines leading to enhanced virulence.  (The package insert of Rapamune states these as contraindications for concomitant use.) |
| 4) Induction of CYP3A4 | anticonvulsants (e.g., carbamazepine, phenobarbital, phenytoin); rifampicin*; rifabutin; foods containing St. John’s Wort (*Hypericum perforatum*) | The products induce CYP3A4 and may lower blood concentrations of the investigational products.  (*Rifampicin induces P-glycoprotein and thus may stimulate removal of the investigational products from cells.) |

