### Laboratory Tests

The principal investigator or subinvestigator will perform the following laboratory tests during the screening phase (V0), Phase I (V1 and V3), Phase II (V5, V6, V7, V8, and V12), follow-up observations (V13), and at discontinuation, and record the results on the electronic case report forms.

[Laboratory test items]

| Tests | Variables |
| --- | --- |
| Hematological tests | red blood cell count, hemoglobin, reticulocyte count, white blood cell count, platelet count, lymphocyte count, neutrophil count, and hematocrit (V0 only) |
| Blood biochemical tests | creatinine, ALP (Changes in the level of ALP will be analyzed as a blood marker), total bilirubin, AST, LDH, ALT, BUN, albumin, CRP, total cholesterol, LDL-cholesterol, uric acid, Na, K, Ca, P, Cl, fasting blood glucose, and serum triglyceride (V0 only) |
| Thyroid hormone tests | FT3, FT4, and TSH (all of these are performed at V1, V5, V12, and discontinuation only) |
| Urinalysis | pH, sugar, protein, and occult blood in urine |
| Viral test | HBs antigen, HBs antibody, HBc antibody, HCV antibody, and HIV antibody (all of these will be performed at V0 only) |
| Thyroid autoantibody tests | TgAb, TPOAb, and TRAb (all of these will be performed at V0 only) |
| Pregnancy test | hCG urine (V0 only) |

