## Discontinuation Criteria

### Participant Withdrawal

The principal investigator or subinvestigator will withdraw a subject from the trial if he/she meets any of the criteria listed below. On withdrawal of the clinical trial, the principal investigator or subinvestigator will immediately secure the safety of the subject and take appropriate measures. When a subject is withdrawn from the clinical trial, reasons for the withdrawal and occurrence of adverse events will be identified and recorded in the source document and on the electronic case report form. Tests that are scheduled at discontinuation will be performed as far as practical.

1) Subject’s request for withdrawal from the trial

2) Subject no longer trackable

3) Discovery of obvious ineligibility for participation in the trial

4) Decision of the principal investigator or subinvestigator that the subject’s participation in the trial would be difficult due to an adverse event that occurs after the initiation of the trial

5) Pregnancy of the subject

6) Death of the subject

7) Need for dosage reduction below the lowest standard of one 1-mg tablet every three days, administered orally

8) Other conditions that the principal investigator or subinvestigator deems appropriate for withdrawal

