# Statistical Analyses

## Populations for Analyses

### Analysis Sets

[Safety]

The safety analysis set will include a set of subjects to whom the investigational products had been administered at least once.

[Efficacy]

1) Full Analysis Set (FAS)

The full analysis set (FAS) will be based on the intention-to-treat (ITT) principle, and will include all patients in this trial other than those who fall under any of the following conditions:

・Violation of eligibility criteria (patients who do not meet main registration criteria for this trial)

・Patients in whom the investigational products had never been administered

・Non-existence of baseline nor treatment data

・Withdrawal of consent during the trial and refusal to allow use of all data

2) Per Protocol Set (PPS)

The Per Protocol Set will include a set of subjects who meet the eligibility criteria for the efficacy analysis based on the standards for subject analysis sets developed before database locking. Eligibility criteria for data to be measured chronologically shall be specified for individual points in time for measurement.

The main analysis set for efficacy in this trial is to be the FAS. For main efficacy endpoints, statistical analysis of the PPS will also be performed. Comparison of the results of two distinctive analysis sets will be used to evaluate the robustness of main analysis results of the trial.

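### The hepatitis B vaccination exception in exclusion criterion 3 names HBs antigen, but the marker that vaccination leaves behind is HBs antibody, which excludes without exception

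*Protocol*

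**What the plan says.** Exclusion criterion 3 appears in the Protocol Summary and in the Study Population section, with the same wording in both. It first lists the grounds for exclusion: "HBs antigen-positive, HBs antibody-positive, HBc antibody-positive, or active hepatitis C". The Study Population section requires that no exclusion criterion be met, so each ground is enough on its own.

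The criterion then makes two exceptions. One concerns hepatitis C: "HCV antibody-positive patients with inactive hepatitis and with normal-range values of liver function do not apply". The other concerns hepatitis B vaccination: "HBs antigen-positive patients for which the cause is presumed to be due to vaccination against hepatitis B may participate in this clinical trial". No sentence exempts a patient who is positive for HBs antibody.

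Section 14.7.3, Laboratory Tests, lists the screening viral tests as "HBs antigen, HBs antibody, HBc antibody, HCV antibody, and HIV antibody (all of these will be performed at V0 only". The rationale under the exclusion criteria gives patient safety, and its proper assessment, as the purpose of criterion 3.

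**The concern.** Vaccination against hepatitis B leaves lasting HBs antibody. HBs antigen is the marker of current infection. The exception therefore lifts a ground that vaccination does not normally trigger, and leaves in force the ground that it does. The sentence is a conditional exception and does not flatly contradict the list before it. The fault is that it names the wrong marker.

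Two things are at stake.

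- **Wrongful exclusion.** A vaccinated candidate with HBs antibody and neither of the other markers is ineligible as written. The trial plans 16 subjects with a rare disease, and section 17.5 gives feasibility as the main consideration in setting that number. If staff follow the presumable intent and enrol such a candidate, they do so against the text. Section 14.11.1 lists "Discovery of obvious ineligibility for participation in the trial" as a ground for withdrawal. Section 17.1.1 removes from the full analysis set any "Violation of eligibility criteria (patients who do not meet main registration criteria for this trial"), which would apply if criterion 3 counts as a main criterion.
- **Wrongful admission.** A candidate positive for HBs antigen can be admitted on a presumption that vaccination is the cause. The protocol's own table of prohibited medications says of the drug: "The immunosuppresive properties of sirolimus may cause proliferation of microorganisms in live vaccines leading to enhanced virulence". Active treatment lasts up to 178 days, and the viral tests are scheduled at V0 only, so no later scheduled test would show the mistake.

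**Working it through.** No statistical figure enters this point, so there is none to reproduce. The check compares the rule as written with the rule as it would read with the other marker, over every combination of results.

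**Are antigen and antibody used as synonyms?** No. Criterion 3 lists them as separate grounds and section 14.7.3 lists them as separate tests. The exception uses only the word antigen, in both places where it appears.

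**Inputs.** Three markers, each positive or negative, give 2 × 2 × 2 = 8 patterns. Vaccination is presumed to be the cause wherever the exception could apply.

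**Rules compared.**

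- As written, narrow reading (the exception lifts only the ground it names): eligible if HBs antibody and HBc antibody are both negative.
- As written, broad reading (the exception lifts the whole criterion for an antigen-positive patient): eligible if HBs antigen is positive, or if all three are negative.
- Corrected (the exception names HBs antibody, with the other two negative): eligible if HBs antigen and HBc antibody are both negative.

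| HBs antigen | HBs antibody | HBc antibody | Written, narrow | Written, broad | Corrected |
|---|---|---|---|---|---|
| − | − | − | in | in | in |
| − | + | − | **out** | **out** | in |
| + | − | − | **in** | **in** | out |
| + | + | − | out | **in** | out |
| − | − | + | out | out | out |
| − | + | + | out | out | out |
| + | − | + | out | **in** | out |
| + | + | + | out | **in** | out |

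Bold marks a result that differs from the corrected rule.

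**Result.** On the narrow reading, 2 of 8 patterns differ: antibody only and antigen only. The other 6, including all 4 with HBc antibody, agree. On the broad reading, 5 of 8 differ: antibody only, and all four antigen-positive patterns, two of which are also HBc antibody-positive. The antibody-only pattern, which is the ordinary result of vaccination, is excluded on both readings.

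On the narrow reading the exception helps only a person who is antigen-positive and has neither antibody, that is, a person who shows no antibody response to the vaccine.

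**The case against.** The strongest reply is that this is a slip, perhaps of translation, whose intent any clinician would recover. The document has other slips of spelling and naming. The eligibility check sheet is not shown and may already carry the right marker. This is plausible, but the two places that state the rule agree with each other, and this is the text that site staff, monitors and the review board work from.

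A second reply is that the safety opening is small. The exception is permissive and needs a presumption of vaccination. Criterion 15 lets the investigator refuse anyone judged unsuitable, and criterion 4 excludes AST or ALT of 100 IU/L or higher. This stands in part: on the narrow reading the route is confined to antigen-positive patients without either antibody. Criterion 4 would still not catch infection with normal enzymes, and on the broad reading the route is wider.

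Third, HBs antigen can be briefly detectable just after a vaccine dose, so the exception is not meaningless. That is granted. It does not explain why the lasting result of vaccination has no exception.

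Fourth, withdrawal and removal from the full analysis set are conditional. They arise only if someone is enrolled against the text, if the ineligibility is judged obvious, and if criterion 3 is a main criterion, a term the protocol does not define. This is correct, and those effects are possible rather than expected.

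Finally, counts of patterns are not frequencies. This is also correct. They show which candidates are misclassified, not how many.

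**Conclusion.** The concern holds. As written, criterion 3 screens out the ordinary vaccinated candidate and can admit an antigen-positive one. It is an eligibility rule with a safety purpose, in a trial whose primary endpoints are safety and tolerability, so it needs correcting.

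Its size is 2 of 8 marker patterns on the narrow reading and 5 of 8 on the broad one, and the antibody-only vaccinee is wrongly excluded on both. The protocol does not say how many candidates fall in any pattern, so no rate can be given. No sample-size, power or analysis figure is affected.

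The conclusion rests on one fact from outside the document, that the lasting marker of hepatitis B vaccination is HBs antibody. This is general immunology. It also assumes that antigen positivity should exclude when vaccination is merely presumed, which is the cautious choice for an immunosuppressive drug.

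**What to change.** In the Protocol Summary and in the Study Population section, change the exception to criterion 3 so that it covers patients positive for HBs antibody whose positivity is presumed to come from hepatitis B vaccination, provided that HBs antigen and HBc antibody are both negative. The added condition also removes the doubt over whether the exception lifts one ground or the whole criterion.

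Then check that the eligibility check sheet agrees. Under Registration of Patients, the investigator "will judge whether patients satisfy the inclusion criteria, based on the assessment during the screening phase, using the eligibility check sheet", so a mismatch there would carry the error into practice.

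The cost is one sentence in two places and one check of a form. All three markers are already measured at V0, so no new test or visit is needed.

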# Endpoints

[Primary Endpoints]

Safety and tolerability:

1) Adverse events (nature, frequency and severity)

2) Side effects (nature, frequency and severity)

3) Clinical laboratory tests

4) Vital signs (blood pressure, pulse, and temperature)

[Secondary Endpoints]

Efficacy:

1) Frequency of hearing loss episodes (number of occurrences/year)

2) Highest measurement of auditory threshold shift at a hearing loss episode (dB)

3) Frequency of dizzy spells (number of occurrences/year)

4) Maximum amplitude (°/sec) and maximum frequency (cycle/sec) of nystagmus during a hearing loss episode

5) Percentage of cases in which increase in hearing threshold was observed during remission in the observation period (comparison of measurements at the end of Phase I and the end of Phase II)

6) Improvement in hearing threshold during remission

7) Shorter duration of hearing loss episodes

8) Alleviation of symptoms of dizziness/vertigo

Changes in total scores of the Dizziness Handicap Inventory from Phase I to Phase II

9) Percentage of cases in which equilibrium exacerbated during remission in the observation period (comparison of measurements at the end of Phase I and the end of Phase II)

[Exploratory Endpoints]

1) Reduction in endolymphatic hydrops (MRI findings)

2) Inhibition of goiter or thyroid enlargement

3) Cell biological changes in thyrocytes detected by cytology tests

4) Comparison of results of in vitro efficacy evaluation of inner ear cells derived from PDS-specific iPS cells and of clinical evaluation

5) Deviation from threshold value for frequency of abnormalities of auditory brain stem responses and for pure-tone audiometry

# Target Study Sample Size

A sample size of 16 subjects is expected to be studied: 12 subjects for the NPC-12T active substance arm, and 4 subjects for the NPC-12T placebo arm.

# Informed Consent Process

## Preparation of Written Information and Consent Form

The principal investigator will prepare a written information and consent form (informed consent form). The informed consent form will be provided as a set of documents consisting of written information and consent document, and will be revised as appropriate.

The informed consent form as prepared or revised will be submitted to the head of the institution for approval by the Institutional Review Board in advance of use.

## Elements to be Included in the Informed Consent Document

The written information shall include the following explanations, at minimum:

1) That the clinical trial involves research

2) The objectives of the clinical trial

3) The names, titles, and contact information of the principal investigator and subinvestigators

4) Clinical trial design, including experimental aspects and the inclusion and exclusion criteria

5) The expected clinical benefits, foreseeable risks, and inconveniences to the patients. If there is no intended clinical benefit to the patient, the patient shall be made aware of that information.

6) The alternative procedures or courses of treatment that may be available to the patient, and their important potential benefits and risks, if the patient is to become a subject

7) The expected duration of the patient's participation in the trial

8) That the patient’s participation in the trial is voluntary and that the patient may refuse to participate or may withdraw from the trial at any time, without penalty or loss of benefits to which the patient is otherwise entitled

9) That, by signing a written informed consent form, the patient will be granting access by the monitors, auditors, the Institutional Review Board, and regulatory authorities to the patient’s original medical records without violating the confidentiality of the patient

10) If the results of the trial are published, the patient’s identity will remain confidential

11) Information on whom to inquire or contact at the institution for further information regarding the trial and the rights of trial subjects, and in the event of trial-related injury

12) The compensation and/or treatments available to the patient in the event of trial-related injury

13) Type of the Institutional Review Board reviewing/deliberating the appropriateness of the clinical trial, etc., matters reviewed/deliberated by each Institutional Review Board, and other matters concerning the Institutional Review Board involved in the clinical trial

14) The approximate number of patients to be participating in the trial

15) That the patient will be informed in a timely manner if information becomes available that may be relevant to the patient’s willingness to continue participation in the trial

16) The foreseeable circumstances and/or reasons under which the patient’s participation in the trial may be terminated

17) The anticipated expenses, if any, to be borne by the patient while participating in the trial

18) The anticipated payment, if any, to made to the patient for participating in the trial

19) Matters that the patient is to comply with

